#### Primary outcome

##### Joint engagement in the parent–child interaction

A semi-structured 12 min videotaped interaction between parent and child will be collected for each dyad at T1, T2 and T3. A standardized set of toys in two boxes (A and B) will be presented. Parents will be asked to engage in free play with box A for four minutes, followed by blowing bubbles for two minutes. Next, parents are asked to repeat the aforementioned, but now with the box B. The videotapes will be coded by observers blind to the group status and scored for the time and quality spend in different engagement states using Joint Engagement Rating Inventory (JERI; [32]). Recordings will be subsequently coded for four engagement states (total joint engagement, supported joint engagement, coordinated joint engagement and symbol-infused joint engagement). The four items are each defined with 7 points providing information about both quantity and quality of engagement states. The low anchor [1] indicates that there are no episodes of joint engagement during the interaction, whereas the high anchor [7] indicates that the child almost always spends time in the joint engagement state during interaction. The midpoint of 4 characterizes a child who is in joint engagement for approximately half of the scene in several brief or a few relatively sustained episodes. Inter-rater reliability between students/research assistants is deemed reliable when there is a minimum of 80% agreement between observers, based on 15% percent of the tapes. The first author (MS) was trained by one of the developers of the JERI until high accuracy was obtained on all four joint engagement states. For the RCT, students and research assistants will be trained by MS in coding video records with use of the JERI.

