**Secondary outcome**				
Change in ASD symptoms	T1, T2, T3	BOSCC (parent)	RA ^b^	Yes
	T1, T3	BOSCC (clinician)	RA^c^	Yes
	T1, T3	ADOS-2	Clinician	Yes
Expressive language	T1, T2, T3	JERI	RA ^b^	Yes
	T1, T3	N-CDI	Parent(s)	
Adaptive functioning	T1, T3	Vineland Screener	Parent(s)	
Parental well-being	T1, T2, T3	WEMWBS	Parent(s)	
	T1, T2, T3	PSQ	Parent(s)	
Parental skills	T1,T2, T3	JERI	RA ^b^	Yes
`Satisfaction	T2	BESTE-O	Parent(s)	
	T2	BESTE-H	BEAR professional	
	T3	Satisfaction survey	Parent(s)	
Cost measurements	T1, T2, T3	Tic-P	Parent(s)	

*Bayley-III* Bayley Scales of Infant and Toddler Development, *BITSEA* Brief Infant–Toddler Social & Emotional Assessment-Revised, *SOV* Dutch version of the Autism Quotient (AQ), *JERI* Joint Engagement Rating Inventory, *BOSCC* Brief Observation of Social Communication Change, *ADOS-2* Autism Diagnostic Observation Schedule, *N-CDI* Dutch version of the MacArthur Communicative Development Inventory, *Vineland Screener* adapted version of the Vineland Adaptive Behaviour Scales, *WEMWBS* Warwick-Edinburgh Mental Well-being Scale, *PSQ* Parenting Stress Questionnaire (PSQ, in Dutch Opvoedingsbelastingsvragenlijst)*, BESTE* the Rating Scale Satisfaction and Effect questionnaire, *Tic-P* Trimbos and iMTA questionnaire on Costs associated with Psychiatric illness

^a^T1 is baseline; T2 is endpoint, eight weeks after baseline; T3 is follow-up, 24 weeks after endpoint

^b^Both the JERI and the BOSCC(parent) are assessed by the BEAR professional as part of the intervention (only at T1 and T2). At T3, both measurements are assessed by a researcher of the SCOPE project. All data will be coded by research assistants who are unaware of treatment allocation

^c^The BOSCC(clinician) is assessed by a professional examiner. Data will be coded by research assistants who are unaware of treatment allocation

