#### Sample size and power

The justification of sample size is calculated based on the primary hypothesis that the BEAR intervention will improve the child’s total joint engagement (measured on a 7-point Likert scale) at the end of treatment. In a comparable study by Kasari et al. [44] with joint engagement as the primary outcome as measured in total seconds spent in joint engagement, a Cohen’s d effect size of 0.21 was found in difference in joint engagement at endpoint. We assume our effect size to be slightly lower than in the study of Kasari et al., due to a shorter duration of the BEAR intervention and the use of an ordinal variable instead of an continuous one. Based on the variance of the treatment effect, a power analysis on an alpha level of 0.05 (two sided) lead to an estimated sample size of 40 participants per group, with a power of 0.88. To allow for 10% drop out 44 participants per group (total *N* = 88) will be recruited.

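### Coders of the primary 7-point rating are accepted on 80% raw agreement, which secures reliability if it means identical scores but not if it means within one point and scores are narrowly spread

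*Protocol article*

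**What the plan says.** The primary outcome is joint engagement, rated from video. Under Joint engagement in the parent–child interaction the article says of the four engagement states: "The four items are each defined with 7 points". Coders, who are students and research assistants, are deemed reliable at "a minimum of 80% agreement between observers, based on 15% percent of the tapes". No kappa, ICC or other chance-corrected coefficient is named. The text does not say whether two scores agree only when identical or also when one point apart, and it gives no SD for the rating.

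The sample size rests on one of the four items, "total joint engagement (measured on a 7-point Likert scale) at the end of treatment". Two safeguards are described. The person who trains the coders was trained by a developer of the instrument "until high accuracy was obtained on all four joint engagement states", and note b to Table 2 states: "All data will be coded by research assistants who are unaware of treatment allocation".

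**The concern.** Percent agreement is a weak test of coders on an ordered scale, for three reasons. It credits agreement that would arise by chance. It treats a one-point miss and a four-point miss alike (or, with a tolerance, counts the one-point miss as a hit). It also depends on the children as much as on the coders: the narrower the spread of scores, the easier 80% is to reach.

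This is the only numerical quality check the article states for the coders of its primary outcome. If it passes coders who hardly separate one child from another, the observed standardised effect shrinks by about the square root of the ICC, and the check gives no warning.

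**Working it through.** The 80% figure is a chosen threshold, so there is no calculation of the plan's to reproduce. The check is which ICC of the recorded 1–7 scores corresponds to 80% agreement.

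**Inputs from the article.** Seven ordered points; 80% threshold; 15% of tapes; 88 dyads filmed at three visits; 40 analysed per group with power 0.88 at two-sided 0.05.

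**Assumed, because the article gives no figure.** Score SD from about 0.57 to 1.8; mean 4; two interchangeable coders whose underlying normal ratings are rounded and clipped to 1–7.

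**Chance agreement.** For independent coders with score probabilities p_k, identical scores occur with probability Σp_k². Scores within one point occur with probability Σp_k(p_{k−1} + p_k + p_{k+1}). A case to check by hand: scores 3, 4, 5 with probabilities 0.25, 0.50, 0.25 (SD 0.71).
- Identical: 0.0625 + 0.25 + 0.0625 = 0.375.
- Within one: 1 − 2 × 0.25 × 0.25 = 0.875. Here the ICC is 0, and the tolerant rule is passed.

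**ICC at which coders just reach 80%.** For interchangeable coders, ICC = 1 − E(d²)/(2·SD²), with d the difference between the two scores.

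| Score SD | Chance, within one | ICC for 80% within one | Chance, identical | ICC for 80% identical |
|---|---|---|---|---|
| 0.57 | 95% | 0 | 52% | 0.69 |
| 0.80 | 83% | 0 | 35% | 0.85 |
| 0.85 | 80% | about 0 | 33% | 0.86 |
| 1.04 | 70% | 0.33 | 27% | 0.91 |
| 1.22 | 62% | 0.52 | 23% | 0.93 |
| 1.27 | 60% | 0.55 | 22% | 0.94 |
| 1.47 | 52% | 0.67 | 18–19% | 0.95 |
| 1.80 | 43% | 0.77 | 15% | above 0.95 |

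The last column can be checked by hand. If 20% of pairs differ, all by one point, E(d²) = 0.20 and ICC = 1 − 0.10/SD². This gives 0.69 at SD 0.57, 0.91 at SD 1.04 and 0.95 at SD 1.47.

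The identical-scores reading has two exceptions. If the disagreeing 20% all differ by two points, E(d²) = 0.80 and ICC = 1 − 0.40/SD², which is 0.60 at SD 1.0. If 90% of children get one score and 10% the next, independent coders agree on 0.81 + 0.01 = 82% with an ICC of 0.

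**Size of the check.** 88 × 3 = 264 tapes at most, and 0.15 × 264 = 39.6, so about 40. A pass needs 32 of 40. By the binomial distribution, coders whose true agreement is 75% pass 30% of the time, and at 70% they pass 11% of the time.

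**Effect on power, as illustration only.** In a simple two-group comparison, 40 per group gives power 0.88 at d = (1.960 + 1.175) × √(2/40) = 0.70. Treat that as the effect without coder error. Power is Φ(0.70 × √ICC × √20 − 1.96).
- ICC 0.75: d = 0.61, power about 77%.
- ICC 0.67: d = 0.57, power about 73%.
- ICC 0.50: d = 0.50, power about 60%.
- ICC 0.33: d = 0.40, power about 44%.

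The 0.70 is not the plan's expected effect. The article cites 0.21 from a comparable trial and expects slightly less. The calculation also ignores clustering and repeated measures, and an effect taken from an earlier trial already carries that trial's coding error. Only the relative loss matters here.

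**The case against.** The strongest reply is that the plain meaning of agreement is identical scores. On that reading 80% is demanding: an ICC near 0.45 yields only 37% identical scores at SD 1.04 and 66% even at SD 0.57, so poor coders are caught. This stands, apart from the two exceptions shown. A reader might infer that the threshold fails on either meaning, too lax on one and impossibly strict on the other. The figures do not support that: a strict criterion does no harm to validity, and 80% identical scores corresponds to an ICC of about 0.7 to 0.95, not to something unattainable.

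A reader might also infer that coders with almost no reliability will pass. That needs both a one-point tolerance and a narrow spread, and the article states neither. The sample may well be varied: children are 12 to 30 months old, both screen-positive children and screen-negative children with concerns are eligible, and tapes span three visits. At SD 1.47, coders with an ICC near 0.48 reach only 69% within one point and fail.

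Nor is bias between arms implied. Coders do not know the allocation, so their errors mainly add noise.

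Finally, the tolerance and the per-item rules may stand in a coding manual that is not shown, and their absence from an article is not in itself a fault. What remains is that the article does fix an acceptance rule for its primary outcome, and that rule is a statistic whose meaning shifts with the spread of scores.

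**Conclusion.** The concern holds in conditional form. With a one-point tolerance and an assumed score SD up to about 1.2, coders with a score ICC of about 0 to 0.5 can be accepted. At SD 1.47 or more, passing requires about 0.67 or higher. With identical scores required, the rule generally secures adequate reliability. The consequence is limited to attenuation by about √ICC and lost power: at an ICC of 0.50 the effect is seen at about 71% of its size, and power of 88% would fall to about 60% in the illustration. Everything here depends on the tolerance and the SD, which the article does not give. The change is worth making because it removes that dependence at almost no cost.

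**What to change.** On the tapes already double-coded (about 40), compute for each JERI item a single-rater absolute-agreement ICC or a quadratic weighted kappa, with its confidence interval. Make a minimum on total joint engagement, fixed before the coefficients are seen, the acceptance criterion; 0.75 is one example. If it is missed, retrain the coders and recode from video, which the Data collection and management section says is stored. Draw the double-coded tapes from all three visits and both arms. Keep percent agreement as description only, and state whether it means identical scores or within one point.

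This needs no extra double coding, only a different statistic on the same tapes. The possible cost is retraining and recoding if the criterion is missed. With about 40 tapes the coefficient will carry some uncertainty, which is why the interval should be reported with it.

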#### Secondary outcomes

##### Social-communicative development

Change in social-communicative development is measured by the measured by the Brief Observation of Social Communication Change (BOSCC; [33]). At T1, T2 and T3, BOSCC will be rated based on the same twelve minutes videotaped parent–child dyadic interaction as the joint engagement measure (BOSCCparent). At T1 and T3, an additional BOSCC will be conducted by a skilled examiner. Here, the child is interacting with a professional examiner who has not been part of the intervention (BOSCCprofessional). The BOSCC consists of 15 coding items associated with key features of ASD, such as making eye contact, unusual sensory interests and the frequency and function of social overtures. The difference in total score between measurement moments is indicative for change in behaviour in the social-communicative domain. The BOSCC is a promising outcome measure and is derived from the Autism Diagnostic Observation Schedule-2 (ADOS-2; [34]) – the “golden standard” measure that has long been used as outcome measure in early intervention studies. Research shows that this new instrument has satisfactory inter-and intra-rater reliability [18, 33]. Next, the ADOS-2 (toddler, module 1 and/or module 2) will be administered at T1 and T3. The ADOS-2 is a semi-structured play observation, where the clinician elicits social, communicative, stereotyped and play behaviour to observe symptoms of ASD. Observations of the clinician are categorized and a score is assigned for each domain of ASD symptoms. Although the ADOS-2 has thus long been considered the “golden standard” in intervention studies, the instrument has its limitations. For example, the ADOS-2 can identify changes in ASD symptoms over a couple of years [3] but due to the narrow range of scores used for each item, the ability to detect subtle changes in behaviour over a shorter time frame might be limited. Also, the ADOS has not been developed to quantify different degrees of autism severity, rather it has been developed to allow for a diagnostic algorithm (yes/no autism). The BOSCC might be more sensitive in detecting subtle changes and better suitable to quantify autism severity. However, since the BOSCC is a relatively new instrument, both instruments will be administered in this study (also enabling future in-depth instrument comparisons).

**Language**

The child’s expressive level of language will be measured by the Dutch adaptation of the MacArthur Communicative Development Inventory: Toddler (N-CDI; Fenson et al., [35, 36]), a parent report, at T1 and T3. Raw scores will be calculated as to indicate both language production and language comprehension. Also, level of expressive language will be measured by using the JERI. Based on the same twelve minute dyadic videotape child’s expressive language level and use will be rated from 1 (no expressive language) to 7 (fluent and frequent use of sentences) at T1, T2 and T3.

**Global level of adaptive functioning**

For estimating global level of adaptive functioning, the Vineland Screener will be conducted at T1 and T3. The Vineland Screener is an adapted Dutch version of the Vineland Adaptive Behaviour Scales (VABS: Sparrow et al., 2005 [37, 38]), consisting of 90 items, to be filled out by one parents/primary caregiver. It consists of the following scales: Communication domain, Daily Skills domain, Socialization domain and Motor Skills domain. Each of the items in the previous mentioned domains contains a statement of child adaptive behavior. Subscales will be calculated as to identify change in global level of adaptive functioning at starting point (T1) and at follow up (T3). Parents themselves rate whether the child mostly (2), sometimes/partly (1) or never (0) performs the behavior or action independently.

**Parental well-being**

Parental well-being is measured by the Warwick-Edinburgh Mental Well-being Scale (WEMWBS; [39]) and Parenting Stress Questionnaire (PSQ, in Dutch Opvoedingsbelastingsvragenlijst, OBVL; [40]). The WEMWBS is a reliable instrument that measures mental well-being. It consists of 14 items, measured on a 5-point Likert type scale and will be completed by both parents/primary caregivers. Additionally, the PSQ is used to determine parental experiences with their child, how they interact with their child and how parents feel about their own health. The PSQ is a well validated and reliable questionnaire that consists of 34 items on a 4-point scale ranging from ‘not true’ to ‘very true’. For both instruments, total scores will be calculated during all measurement points.

**Parental skills**

Parental intervention skills, or parental fidelity is defined as “to execute parent-implemented techniques accurately and consistently” [41]. By measuring parental skills, investigators document that parents can indeed perform the intervention techniques as they were intended to be used. These skills will be rated by the parent scales of the JERI and consists of four items covering caregivers’ scaffolding, symbol highlighting, following in on child’s focus and caregivers’ affect. The scaffolding item assesses how well the parent supports the child’s activities and provides learning opportunities. Symbol highlighting focuses on how often the caregiver directs the child’s attention to symbols (language and/or symbolic gestures and acts). Following in on child’s focus captures if the parent is following the child’s interests and maintain focus with the child. Finally, caregivers’ affect measures the parent’s affect and how it influences the parent–child interaction [32]. Items fit the techniques taught by the BEAR intervention. Just as with the joint engagement items, parent scale items will be rated from a scale of 1 to 7. Parental skills will be rated based on the same videotaped dyadic interaction as the joint engagement measure, as collected at baseline, end of treatment and follow-up. Also, in order to capture the flow of interaction between parent and child, an interaction item (fluency and connectedness) will be scored.

**Parental satisfaction**

Parental satisfaction with care in general is measured at follow-up through a survey created by our group. The full survey can be found in the supplementary materials (Additional file 1: Appendix A). Topic items included initial concerns, searching for help, receiving a diagnosis, child and parent treatment and overall satisfaction with the healthcare process. To measure parental satisfaction specifically for the BEAR intervention specifically, the Rating Scale Satisfaction and Effect questionnaire (in Dutch: Beoordelingsschaal Tevredenheid en Effect [BESTE]; [42]) will be conducted. The BESTE consists of two versions: one for parents and one for healthcare practitioners, and both versions will be administered. Validity and reliability have been established [42]. The BESTE will only be conducted end of treatment, and in the BEAR condition only. Descriptive statistics will be used to present percentages regarding satisfaction and effect, as mentioned by both parents and practitioners.

**Assessment of healthcare sources**

Direct and indirect costs as a consequence of the child’s psychiatric condition, i.e. the medical costs and productivity losses in parents are measured using the ‘Trimbos and iMTA questionnaire on Costs associated with Psychiatric illness’ (Tic-P questionnaire; [43]). Validity and reliability have been established [43]. For every participant, the duration and type of each contact as well as the type of health care worker with whom the contact was in the last 3 months will be registered as to monitor use of healthcare sources in both groups as well as to calculate the cost-effectiveness of arms. Productivity losses of parents associated with their child’s health problem or its treatment will be registered as well.

#### Sample size and power

The justification of sample size is calculated based on the primary hypothesis that the BEAR intervention will improve the child’s total joint engagement (measured on a 7-point Likert scale) at the end of treatment. In a comparable study by Kasari et al. [44] with joint engagement as the primary outcome as measured in total seconds spent in joint engagement, a Cohen’s d effect size of 0.21 was found in difference in joint engagement at endpoint. We assume our effect size to be slightly lower than in the study of Kasari et al., due to a shorter duration of the BEAR intervention and the use of an ordinal variable instead of an continuous one. Based on the variance of the treatment effect, a power analysis on an alpha level of 0.05 (two sided) lead to an estimated sample size of 40 participants per group, with a power of 0.88. To allow for 10% drop out 44 participants per group (total *N* = 88) will be recruited.

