### Cluster randomized controlled trial

#### Study design and randomization

The effectiveness of the BEAR intervention will be studied in a two-armed cluster RCT (ratio 44:44). Well-baby clinic locations in the Nijmegen area in the Netherlands will be randomly assigned to either the BEAR or Care-as-usual (CAU) condition. Before randomization, the well-baby clinics will first be matched based on two characteristics (amount of children visiting that well-baby clinic and ethnicity/social-economic background of the specific area) to ensure an equal distribution in the two groups. By coin flipping, the well-baby clinics are at random assigned to either the BEAR condition or CAU. Consequently, the study is open-labeled; both participants (children and parents) and the therapist know to which condition the participant is assigned through cluster randomization. However, for the primary outcome measure, our assessors rating parent–child interaction are unaware of group allocation (see Table 2).

**Table 2 Tab2:** Outcome measures from baseline to follow-up

Measurement	Time^a^	Instrument	Informant	Blind to group status?

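### The stated power of 0.88 with 40 per group does not follow from an effect at or below d = 0.21; at that effect, power is about 15%

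*Protocol article*

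**What the plan says.** All the figures are in the Protocol article, Sample size and power.

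- **Target:** the hypothesis that BEAR will "improve the child’s total joint engagement (measured on a 7-point Likert scale) at the end of treatment".
- **Reference effect:** in a comparable trial "a Cohen’s d effect size of 0.21 was found in difference in joint engagement at endpoint".
- **Assumed effect:** no number is given, only a direction: "We assume our effect size to be slightly lower than in the study of" that trial. The reasons offered are the shorter intervention and the ordinal outcome.
- **Test:** "a power analysis on an alpha level of 0.05 (two sided").
- **Result:** the calculation is said to "lead to an estimated sample size of 40 participants per group, with a power of 0.88".
- **Recruitment:** "To allow for 10% drop out 44 participants per group", 88 in total.

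The calculation is also described as "Based on the variance of the treatment effect", but no variance, SD, baseline correlation or intracluster correlation is given. Study design and randomization describes a "two-armed cluster RCT (ratio 44:44"), with well-baby clinics as the randomised units.

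**The concern.** An effect of about a fifth of a standard deviation is small. Detecting it with high power ordinarily takes several hundred participants per arm, so 40 per arm with 0.88 power is suspect on sight. The objection is to a contradiction between printed numbers, not to missing detail.

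This is the trial's only power statement and it supports its only primary outcome. If BEAR has the effect the plan assumes, the trial will more often than not give a non-significant result. A reader who has been told that power was 0.88 could then take that result as evidence that BEAR does not work. If the design was really built to detect a much larger effect, the text misreports its own target.

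**Working it through.** **Inputs from the Protocol article:** d = 0.21 or slightly lower; n = 40 per group; two-sided alpha 0.05; stated power 0.88. Because d is already standardised, the SD is 1.

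**1. Attempt to reproduce 0.88.** For two independent groups the noncentrality is d × √(n/2), and with n = 40, √20 = 4.472. At d = 0.21 this is 0.21 × 4.472 = 0.939. By the normal approximation, power = Φ(0.939 − 1.960) = Φ(−1.021) = 0.154. The exact noncentral t (78 df) gives 0.153.

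| d | Power, 40 per group (noncentral t) | n per group for 0.88 power |
|---|---|---|
| 0.21 | 0.153 | 447 |
| 0.20 | 0.143 | about 492 |
| 0.18 | 0.125 | about 608 |

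The last column follows from n = 2 × (1.960 + 1.175)² / d². At d = 0.21 this is 2 × 9.828 / 0.0441 = 445.7, so 446 per group; the t-based figure is 446.7, so 447.

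**2. Effect that 0.88 implies.** d = (1.960 + 1.175) / 4.472 = 0.701 (normal), or 0.710 (noncentral t). Against the cited value, 0.710 / 0.21 = 3.4.

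**3. Other simple readings at d = 0.21.** One-sided test: 0.24. All 44 per group retained: 0.164 (t). One-sample formula: 0.26 with 40 and 0.47 with 80. None approaches 0.88.

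**4. Baseline adjustment.** The planned mixed model includes baseline covariates. Adjustment divides the SD by 1/√(1 − ρ²), so the effective d is d / √(1 − ρ²). The article gives no ρ, so these values are assumptions (normal approximation, d = 0.21):

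| ρ | 0.5 | 0.7 | 0.8 | 0.9 |
|---|---|---|---|---|
| Power | 0.19 | 0.26 | 0.35 | 0.58 |

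Reaching 0.88 needs √(1 − ρ²) = 0.21 / 0.710, so ρ = 0.955.

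**5. Clustering.** The article gives no intracluster correlation or cluster size. Assuming an ICC of 0.01 to 0.05 and 4 to 8 children per cluster, the design effect 1 + (m − 1) × ICC runs from 1.03 to 1.35. The unadjusted power at d = 0.21 falls from 0.154 to between 0.150 and 0.125. The detectable d at 0.88 power rises from 0.71 to between 0.71 × √1.03 = 0.72 and 0.71 × √1.35 = 0.82.

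**6. A possible origin of 0.88.** In a group-by-time F test with N = 80 and two measurements, the noncentrality is f² × N × 2 / (1 − ρ). With Cohen's f = 0.177 and ρ = 0.5 it is 0.0313 × 160 / 0.5 = 10.0, which gives power 0.88. So does f = 0.21 with ρ = 0.3 (0.0441 × 160 / 0.7 = 10.1). In a 2 × 2 layout f corresponds to a difference in change of 4f SD: 4 × 0.177 = 0.71 SD, or 4 × 0.21 = 0.84 SD. A value near 0.2 entered as f instead of d would therefore yield the printed power, but for an effect three to four times as large as the one cited.

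**The case against.** The strongest reply is that 15% is not the power of the planned analysis. The plan is a repeated-measures mixed model with baseline covariates, and 15% belongs to an unadjusted comparison at endpoint. That is correct, and the fair statement is a range: about 0.19 to 0.35 for assumed baseline correlations of 0.5 to 0.8, before clustering takes some of it back. It also means 0.88 is not strictly impossible, since a correlation of 0.955 would deliver it. But the article states no such correlation, and one that high is not credible for a 7-point observer rating for which 80% inter-rater agreement is accepted.

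A second reply is that the article condenses a fuller protocol, and that the reference to a variance may point to a valid input that was not printed. The printed d of 0.21 would then be the error, and the calculation sound. This cannot be excluded. It moves the error without removing it: the paragraph would misstate the effect that the trial is designed to detect.

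Third, the Cohen's f explanation is inference. The article names only d, and with f, the correlation and the number of measurements all free, several combinations land near 0.88 (for example f = 0.19, ρ = 0.3, three measurements: 0.887). It is a lead for the authors to check, and the finding does not depend on it.

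**Conclusion.** The concern holds. The stated power does not follow from the stated effect, sample size and alpha, and nothing elsewhere in the article repairs it. At d = 0.21 the gap is 0.88 against 0.153, about 73 percentage points, or 447 / 40 = about 11 times the sample size. An assumed effect slightly below 0.21 widens it.

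The 0.153 rests only on the article's own inputs and a standard two-group comparison. The adjusted and clustered figures rest on assumed correlations, ICCs and cluster sizes, and under every plausible choice power stays far below 0.88. If the true effect is 0.21, the chance of a non-significant primary result is about 85% unadjusted, and about 65% to 81% with baseline correlations of 0.5 to 0.8. This must be corrected.

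**What to change.** Keep N = 88 and rewrite the Sample size and power paragraph, with the same correction in the SAP:

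- State that 40 evaluable participants per group give 0.88 power, before clustering, only for d of about 0.71, and about 15% power for the cited d = 0.21 in an unadjusted comparison.
- Name the effect size, its metric and the variance or correlation actually entered. If 0.21 was Cohen's f or another measure, say so and convert it to a difference in JERI points.
- State the ICC and cluster size assumed, and give the power or detectable effect with clustering included.
- Preferably, commit to reading a non-significant primary result through its confidence interval and not as evidence of no effect. This is good practice and not essential to the correction.

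The cost is the rewording of one paragraph and the matching SAP text. The published power becomes much less favourable, but no participant, visit or treatment changes.
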